### Data coordination and site management

Data coordination and site management services will be performed at the Cardiovascular Center of the Korea University Guro Hospital.

### Timeline

A SENS-ILIAC trial timeline description is presented in Additional file 3.

## Discussion

A primary endovascular approach may be attempted in all patients with peripheral artery obstructive disease including iliac lesions. In performing endovascular repair for iliac artery lesion, different strategies and types of stents are needed, as described above. There is no general consensus on which stents, balloon-expandable or self-expandable stents are the most appropriate for specific lesion of the iliac artery.

The factors associated with patency after stent implantation in iliac lesion have been known to be various: patient characteristics, lesion characteristics, and so on. Recently, various self-expandable nitinol stents have been manufactured with improved radial force, reduced stent deformity or fracture, and convenient deployment systems. Currently, self-expandable nitinol stents have been the most widely used.

The next-generation balloon-expandable stent has been developed. The first Assurant® balloon-expandable stent system (Medtronic, Inc., Santa Rosa, CA, USA) made from a cobalt-chromium alloy is to be approved by the Food and Drug Administration (FDA) for the treatment of narrowed iliac arteries. The mechanical properties of the cobalt-chromium alloy allow the device to have thinner struts and a low profile, which provide increased flexibility while maintaining radial strength and fluoroscopic visibility [27]. In the ACTIVE study [25], the balloon-expandable Assurant® cobalt-chromium iliac stent demonstrated primary patency at 9 months of 99.2 %, device and lesion success were each 97.5 % (155/159), and the procedural success was 96.7 %.

In real-world clinical practice, physicians tend to deploy self-expanding stents in the mid-iliac area due to severe angulation and tortuosity for fear of iliac artery injury including extravasation, dissection, or rupture following high-pressure balloon inflation with longer balloon-expandable stents. It will be of interest to see the safety rate of balloon-expandable stents in the tortuous mid-iliac artery.

However, because of the possibility of ‘geographic miss’- by stent elongation or jumping during stent deployment - which may cause stent fracture, in-stent restenosis, and contralateral artery flow limitation, the balloon-expandable stent has been recommended for accurate stent deployment, especially in bifurcation lesion, including common iliac artery ostium. It will also be important to compare the geographic miss rate between the balloon-expandable SCUBA stents and self-expandable COMPLETE-SE™ stents in iliac artery lesion, especially aortoiliac bifurcation lesion.

One of the significant limitations to previous studies is that they were nonrandomized studies of relatively small sample size, indirect comparisons, or expert opinions. To date, a multicenter, randomized controlled trial for direct comparison of efficacy and safety between self-expandable stents and balloon-expandable stents has not been done.

This trial was designed to evaluate the efficacy and safety between self-expandable COMPLETE-SE™ versus balloon-expandable SCUBA™ stents in patients undergoing stent implantation in iliac artery lesions and will provide a rationale for which choice of stent will be optimal in iliac steno-occlusive disease, particularly with regard to accurate lesion location.

In conclusion, we still do not know whether there is a difference in primary patency, incidence of geographic miss, and stent fracture between self-expandable nitinol stents and balloon-expandable cobalt-chromium stents (COMPLETE-SE™ versus SCUBA™) in stenotic or occlusive iliac arterial lesion. We hope to address these issues in the SENS-ILIAC trial where we have enrolled a large unselected population of patients treated with stent implantation for significant iliac arterial disease.

## Trial status

This study is ongoing and is recruiting.

## Abbreviations

ABI, ankle-brachial index; CEAC, Clinical Event Adjudication Committee; CIRI, Cardiovascular Intervention Research Institute; CLI, critical limb ischemia; CT, computed tomography; CTO, chronic total occlusion; DSMB, Data and Safety Monitoring Board; FDA, Food and Drug Administration; Hct, hematocrit; Hgb, hemoglobin; MACE, major adverse cardiovascular event; MLD, minimal luminal diameter; PCI, percutaneous coronary intervention; PSVR, peak systolic velocity ratio; PTA, percutaneous transluminal angioplasty; QCA, quantitative coronary angiography; RVD, reference vessel diameter; SFA, superficial femoral artery; TASC, TransAtlantic Inter-Society Consensus; TER, target extremity revascularization; TLR, target lesion revascularization

## Appendix

### 1. End points definitions

- Primary patency: defined as stenosis of at least 50 % of the luminal diameter according to the worst angiographic view at the narrowest site within the treated segment plus the 10-mm segments proximal and distal to the treated segment by catheter angiography or CT angiography; PSVR ≥2.5 (PSVR = peak systolic velocity within the area of stenosis divided by peak systolic velocity in a normal adjacent proximal artery segment) or total occlusion by duplex ultrasound
- Geographic miss according miss grade (mild, moderate, severe): geographic miss is classified as 5–15 mm (mild), 15–25 mm (moderate), >25 mm (severe), or additional stent deployment over the stent deployment area that was not covered, or protrusion from the intended stent deployment area
- Stent fracture rate according fracture grade (minor, moderate, severe), [28] plain X-ray examinations for the stent fracture are used or performed using at least two different angulations (30 to 45° difference) and the highest available magnification. Stent fracture is classified as minor (single strut fracture), moderate (fracture of more than two struts), or severe (complete separation of stent segments)
- Target lesion revascularization (TLR): defined as any repeat percutaneous intervention of the target lesion or bypass surgery of the target vessel performed for restenosis because of a return of ischemic symptoms, decrease of at least one Rutherford category, decrease in the ankle brachial index of >0.15, or restenosis of >50 % as measured by catheter angiography. The target lesion is defined as the treated segment from 10 mm proximal to the stent and to 10 mm distal to the stent
- Target extremity revascularization (TER): defined as any repeat percutaneous intervention of the target extremity or bypass surgery of the target extremity performed for restenosis because of a return of ischemic symptoms, decrease of at least one Rutherford category, decrease in the ankle brachial index of >0.15, or restenosis of >50 % as measured by catheter angiography
- Limb salvage: defined as survival free of amputation. Amputation is defined as above-ankle amputation of the index limb
- Sustained clinical improvement rate [29, 30] defined as persistent ABI value ≥0.15 and persistent improvement of ≥1 class according to Rutherford throughout follow-up when compared with baseline without the need for repeat TLR in surviving patients. Late loss: defined as a change in MLD from final angiogram to follow-up
- Major adverse cardiac events (MACE): defined as composite of all-cause death, myocardial infarction, cerebrovascular stroke, and target lesion revascularization

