### Randomization and interventions

Prior to the endovascular intervention, informed consent (see Additional file 2) will be obtained from all participants by investigators. Aspirin and clopidogrel will be administered at least 12 hours before the procedure. Prior to the intervention, 70 to 100 units/kg of unfractionated heparin will be administered. Endovascular interventions will be carried out percutaneously, by placing a 6–8Fr sheath at the femoral artery via an antegrade approach or a contralateral crossover technique. In selected cases, a retrograde approach (from the distal superficial femoral artery (SFA), popliteal artery, or pedal arteries) and/or brachial approach will be allowed. Diagnostic angiography will be performed in two different views at least 30 to 45° apart to evaluate the structure of the target lesion. Femoropopliteal and tibial arteries will be visually checked for the presence of distal lesions. To document the precise location of the lesion and the site of the intervention, we will recommend the use of a ruler. In cases of total occlusion, both intraluminal and subintimal methods of recanalization will be allowed. During the procedure, the use of other special devices will be allowed; for example reentry devices OUTBACK™ catheters (Cordis Corp., Miami Lakes, FL, USA) and Offroad catheters (Boston Scientific, Natick, MA, USA), chronic total occlusion (CTO) devices Frontrunner (Cordis Corp., Miami Lakes, FL, USA) and Truepath (Boston Scientific, Natick, MA, USA), and atherectomy devices such as SilverHawk™ and TurboHawk™ (Covidien, Plymouth, MN, USA). After the successful passage of the guidewire, predilation of the target lesion with an optimally sized balloon will be performed prior to stent implantation. Recommended minimal balloon dilation time is 120 seconds. Then, if there is a residual pressure gradient of ≥10 mmHg, residual stenosis of ≥30 %, or flow-limiting dissection, the balloon angioplasty results will be considered as suboptimal results. Subsequently, web-based randomization for stent selection will be performed. Patients will be randomly allocated to one of two groups, the balloon-expandable or self-expandable stent group, according to the stent deployment method. Random allocation of the patients will be performed via a web-based computerized program separately managed at the Cardiovascular Intervention Research Institute (CIRI), Korea University Guro Hospital, Seoul, Republic of Korea. Patients will be randomized in a 1:1 manner according to two different stents (SCUBA™ versus COMPLETE-SE™). The stents will be implanted to extend 10 mm proximally and distally from the margins of the target lesion with luminal narrowing of ≥50 %. A proper stent size will be selected after review of the baseline angiography results. If the stent is randomized to the COMPLETE-SE™, a stent with a diameter 1 to 2 mm larger than that of the true vessel lumen will be selected. However, if the stent is randomized to the SCUBA™ stent, a stent of equal size to the reference vessel diameter will be selected to prevent iliac artery injury. Spot stenting or full lesion coverage will be decided at the physician’s discretion. When multiple stents are required, the margins of the stents should be overlapped by at least 10 mm. Adjuvant postdilation after the stenting will be performed strictly within the stented segment, with up to 10 % oversizing of the postdilation balloon.

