
The self-expandable COMPLETE-SE™ stent has three distinct crown configurations, and an alternating connection pattern minimizes crown-to-crown interaction and provides optimal flexibility, foreshortening, and lesion coverage for each stent size. The triaxial deployment design includes an inner shaft, a retractable sheath, and a stabilizing sheath, which reduces friction and allows the retractable sheath to move back freely. This decreases the amount of force required to deploy the stent, making deployment easy and accurate. Diameter and length of self-expandable COMPLETE-SE™ stents are 5–10 mm and 20, 40, 60, 80, 100, 120, and 150 mm, respectively. Balloon-expandable SCUBA stents are composed of thin cobalt-chromium struts, unlike other stainless steel stents, and have a closed-cell design for tight scaffolding and appropriate radial strength in iliac lesions. Diameter and length of balloon-expandable SCUBA™ stents are 6–10 mm and 20, 30, 40, and 60 mm, respectively. The entire stent size (the COMPLETE-SE™ and SCUBA™ stent) is now 6-Fr sheath compatible. We will use either a 0.035” or 0.018” wire system and implant either a SCUBA™ or COMPLETE-SE™ stent. All ipsilateral femoropopliteal arterial lesions should be treated with angioplasty and/or stenting concomitantly and residual stenosis should be less than 50 %. Treatment of tibioperoneal lesions is recommended only in cases of CLI. There should exist at least one patent (<50 % stenosis) tibioperoneal run-off vessel with good antegrade flow. A final angiography will be performed after the intervention in both groups, with the use of the same angles and magnifications used at the baseline angiograms. Simultaneously, reference vessel diameter (RVD), minimal luminal diameter (MLD), percent diameter stenosis, and acute gain should be measured. The RVD will be obtained from averaging 5-mm segments proximal and distal to the lesion. Technical success will be defined as successful access, deployment of the stent, and less than 30 % diameter residual stenosis after the revascularization. For postprocedural medication, aspirin 100 mg and clopidogrel 75 mg will be administered once daily for at least 12 months. Cilostazol would be permitted as the third antiplatelet at the physician’s discretion. After enrollment and index procedure, clinical follow-up will be planned at 1, 6, and 12 months to evaluate clinical outcomes and ankle-brachial index (ABI) score. In addition, a follow-up catheter angiography, CT angiography, or duplex ultrasound will be recommended to all patients at 12 months, according to local clinical practice. The investigators will be urged to follow up on patients, either by office visits or by telephone contacts, as necessary. Patient adherence to the study drug and side effects will be checked and monitored at every outpatient visit. The decision of drug discontinuation will be discussed and checked at the physician’s recommendation.

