### Statistical analysis

The IBM SPSS 20.0 (IBM Corp., Armonk, NY, USA) statistics program will be used for all analysis. Categorical variables will be expressed as delivery rate when comparing baseline features between the SCUBA™ and COMPLETE-SE™ stent groups and for categorical variables, comparisons between groups will use the chi-square or Fisher’s exact test. Continuous variables will be expressed as mean ± standard deviation, and for continuous variables, comparisons between groups will use the Student’s *t* test. The primary and secondary end points will be analyzed using both intention-to-treat analysis (all subjects assigned to a treatment group) and per protocol analysis (only subjects who completed the treatment protocol). Noninferiority will be considered proven if conclusions drawn from the intention-to-treat and per protocol analyses are consistent. Balloon-expandable stent patency will be judged as noninferior to that of the self-expandable stent when the lower limit of the 95 % CI of the difference between the proportions of patent patients at 1 year in both groups is higher than -δ = −10 % At the end of the 12 months, cumulative restenosis rates will be calculated. For a secondary end point, we will summarize with descriptive statistics and compare between treatment groups using the Student’s *t* test, chi-square test, or Fisher’s exact test. Also, clinical outcomes such as revascularization of the target vessel, death, major cardiovascular events including myocardial infarction and cerebral infarction, and limb salvage rates will be analyzed using Kaplan-Meier survival estimates and a comparison of the groups will be performed using the log-rank test. A *P* value <0.05 will be considered to be statistically significant. In order to evaluate the risk factors for recurrence, defined as restenosis or total occlusion, univariate and multivariate logistic regression analysis will be performed. The present research has concluded that there will be a very low chance of missing data to cause bias, and therefore, missing data for the major end points will be excluded from the analysis data.

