#### Clinical Event Adjudication Committee (CEAC)

The Clinical Event Adjudication Committee (CEAC) is comprised of interventional and noninterventional cardiologists who are not involved in the study. The CEAC is charged with the development of specific criteria used for the categorization of clinical events and clinical end points in the study, which are based on protocol. At the onset of the trial, the CEAC will establish explicit rules outlining the minimum amount of data required and the algorithm to be followed in order to classify a clinical event. All members of the CEAC will be blinded to the primary results of the trial. The CEAC will meet regularly to review and adjudicate all clinical events. The CEAC will also review and rule on all deaths that occur throughout the trial.

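### TLR and TER count re-treatment of a symptom-free restenosis, a decision made by operators who know the stent, so these secondary comparisons can be biased if re-treatment habits differ by arm

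*Protocol article*

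**What the plan says.** The Appendix (section 1, End points definitions) counts as TLR a repeat percutaneous intervention of the target lesion, or bypass of the target vessel, "performed for restenosis because of a return of ischemic symptoms, decrease of at least one Rutherford category", an ABI fall of more than 0.15, "or restenosis of >50 % as measured by catheter angiography". TER uses the same list for the whole extremity. The article defines no separate clinically driven TLR or TER.

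Four other places bear on how this works:

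- **Imaging** (Randomization and interventions): "a follow-up catheter angiography, CT angiography, or duplex ultrasound will be recommended to all patients at 12 months, according to local clinical practice".
- **Knowledge of the arm** (same section): allocation comes during the procedure, after a suboptimal balloon result: "Subsequently, web-based randomization for stent selection will be performed". Sizing then depends on the arm; for SCUBA, "a stent of equal size to the reference vessel diameter will be selected", while COMPLETE-SE is oversized by 1 to 2 mm.
- **Adjudication** (Clinical Event Adjudication Committee): "The CEAC will meet regularly to review and adjudicate all clinical events". The members are said to be blinded to the trial's primary results. Blinding to the stent arm is not stated.
- **Use of TLR elsewhere**: TLR and TER are secondary end points 5 and 6. Sustained clinical improvement is judged "when compared with baseline without the need for repeat TLR in surviving patients". The Appendix version of MACE includes TLR; the version under Outcome measures has repeat PCI instead. The Statistical analysis section compares "clinical outcomes such as revascularization of the target vessel" between arms by Kaplan-Meier and log-rank.

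**The concern.** A revascularization end point is usually read as clinical failure of the treated segment. Here it mixes two things: re-treatment because the patient got worse, and re-treatment because a narrowing was seen on an angiogram. The first is anchored to the patient's condition. The second depends on whether someone who knows the stent chooses to treat a lesion that is causing no trouble.

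Scheduled imaging of all patients at 12 months creates the occasions for such decisions, most directly at sites that use catheter angiography and already have the patient on the table. If operators are readier to re-treat one stent type than the other, two stents with the same true restenosis will show different TLR rates. The difference passes to TER, to sustained clinical improvement and to MACE as the Appendix defines it. Event adjudication does not remove it, because a symptom-free re-treatment satisfies the written definition and has to be accepted.

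**Working it through.** The article gives no TLR or TER rate, event count or power, so there is no figure of its own to reproduce. The check has three steps.

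**1. Reading the definition.** The indications form one list ending in *or*. Symptoms, Rutherford change and ABI fall are alternatives, so the angiographic finding is enough alone. TER has the same wording.

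**2. Size of the discretionary pool.** Inputs from Sample size calculation: 120 evaluable patients per group; expected patency 90% (self-expandable) and 88% (balloon-expandable), so 10-12% lose patency. Assumed, because the article does not give it: 25-75% of these lesions are symptom-free.

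- Lesions per arm: 120 × 0.10 = 12.0; 120 × 0.12 = 14.4.
- Symptom-free, low end: 12.0 × 0.25 = 3.0 patients, or 3.0/120 = 2.5%.
- Symptom-free, high end: 14.4 × 0.75 = 10.8 patients, or 10.8/120 = 9.0%.

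So about 3-11 patients per arm may or may not become TLR events by choice.

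**3. What an arm difference would take.** Let R be the restenosis rate, s the symptomatic share (all re-treated), c the share of symptom-free lesions that reach catheter angiography, and q the probability that such a lesion is then re-treated. Only R comes from the article; s, c and q are assumed.

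Counted TLR = R·s + R·(1 − s)·c·q

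With R, s and c equal in both arms, the difference between arms is R·(1 − s)·c·(q₁ − q₂). It is zero if q is the same in both. Take R = 10%, s = 50%, and q = 25% in one arm against 75% in the other. Standard errors use the usual formula for a difference of two proportions with 120 per arm.

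| c | TLR, q = 25% | TLR, q = 75% | Difference (points) | Standard error (points) |
|---|---|---|---|---|
| 50% | 5.0 + 5.0 × 0.5 × 0.25 = 5.6% | 5.0 + 5.0 × 0.5 × 0.75 = 6.9% | 1.25 | 3.1 |
| 90% | 5.0 + 5.0 × 0.9 × 0.25 = 6.1% | 5.0 + 5.0 × 0.9 × 0.75 = 8.4% | 2.25 | 3.3 |
| 100% | 5.0 + 5.0 × 0.25 = 6.25% | 5.0 + 5.0 × 0.75 = 8.75% | 2.5 | 3.4 |

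Across wider assumptions, with the same threefold contrast in q, the difference runs from 10% × 0.3 × 0.1 × 0.5 = 0.15 points (R = 10%, s = 70%, c = 10%) to 12% × 0.7 × 0.9 × 0.5 = 3.8 points (R = 12%, s = 30%, c = 90%).

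If only clinically driven re-treatment counts, the formula reduces to R·s. At R = 10% and s = 50% that is 5.0% in both arms, whatever c and q are.

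**The case against.** The strongest reply is that the definition is explicit, identical in both arms and contradicts nothing, so preferring clinically driven TLR is advice and not a correction. Several parts of that reply stand and limit the point.

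- **These are still stent failures.** A reader might infer that the rates would reflect operator behaviour instead of stent failure. They would not: a restenosis of more than 50% must be present, and the trial itself treats that as loss of patency. What is discretionary is whether it is found and re-treated.
- **The modality restriction matters little.** Naming only catheter angiography might suggest that lesions found on CT or duplex escape the count. But TLR counts interventions, and a lesion sent for re-treatment will usually be measured by catheter angiography then, and so qualify. Modality can change how likely re-treatment is, but seldom whether it counts.
- **Local imaging practice is not an arm effect.** It follows the site, not the stent, and mainly moves both arms together. A difference needs arm-dependent decisions, and nothing in the article shows that these occur.
- **The reach is limited.** TLR and TER are secondary. The MACE definition under Outcome measures does not contain TLR, and the log-rank sentence speaks of the target vessel without naming TLR or TER. Clustering of events near month 12 does not invalidate a log-rank test when both arms share one schedule.
- **The committee's own criteria**, which are not shown, may already sort events by indication.

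The last item does not dispose of the point. Sorting events by indication does not change which event the article says will be compared. The operator's knowledge of the stent is inferred from the procedure and not stated in so many words, but the inference is secure.

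**Conclusion.** The point holds as a limited weakness in secondary end points. The definition admits re-treatment of symptom-free restenosis, and the decision is taken by people who know the stent. If re-treatment decisions differ by arm, TLR, TER, sustained clinical improvement and the Appendix version of MACE are biased. The primary noninferiority test is not affected, because the patency definition does not include TLR.

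About 3-11 patients per arm (2.5-9% of 120) are open to discretion, given the plan's patency rates and an assumed symptom-free share of 25-75%. It would be wrong to read those 2.5-9 points as bias between arms: they are the swing in one arm's rate between treating none and treating all such lesions. Even a threefold contrast in re-treatment gives 1.25-2.5 points in the central illustration, which is less than one standard error. That would seldom decide a comparison alone, but it is avoidable.

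**What to change.** Make clinically driven TLR and TER the compared end points: repeat intervention for restenosis found by any of the listed modalities, together with returned ischemic symptoms, Rutherford worsening or the stated ABI fall. The text should say worsening, because the present wording speaks of a decrease while the inclusion criteria use higher Rutherford scores for more severe disease.

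- Have the existing adjudication committee classify the indication without knowledge of the stent arm where feasible.
- Use the clinically driven component in sustained clinical improvement, and in MACE wherever TLR is retained once the two MACE definitions are reconciled.
- Report any TLR and any TER as supportive, flagging re-treatment prompted only by the scheduled 12-month imaging.

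This changes what is counted, not when a patient is re-treated.

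The cost is revised Appendix wording and one indication field. Rutherford and ABI data are already needed for the other secondary end points, and the article describes the trial as still recruiting. The downside is fewer events and so less precision. A residual limit remains: symptom reports and the choice to treat a symptomatic patient are also made with the stent known. The change narrows the room for discretion but does not close it.

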### 2. Immediate outcomes

- Acute lesion success: defined as a residual stenosis of ≤30 % without flow-limiting dissection in the worst angiographic view
- Definition of suboptimal result: residual pressure gradient of >15 mmHg, residual stenosis of >30 %, or flow-limiting dissection
- Acute hemodynamic success: defined as a ≥0.15 improvement in the ankle-brachial index from preprocedure to immediately postprocedure (discharge)
- Clinical success: defined as an improvement of baseline symptoms by at least one Rutherford category that was sustained throughout follow-up with no additional intervention

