### 5. An episode of bleeding is defined by the Thrombolysis in Myocardial Infarction (TIMI) criteria as:

- Major: overt clinical bleeding (or documented intracranial or retroperitoneal hemorrhage) associated with a drop in hemoglobin (Hgb) of greater than 5 g/dl (0.5 g/l) or in hematocrit (Hct) of greater than 15 % (absolute) ^*^Note: a patient who experiences an intracranial hemorrhage should be considered to have a major hemorrhage
- Minor: overt clinical bleeding associated with a fall in hemoglobin of 3 to less than or equal to 5 g/dl (0.5 g/l) or in hematocrit of 9 % to less than or equal to 15 % (absolute)
- None: no bleeding event that meets the major or minor definition

^*^Note: in calculating the fall in hemoglobin or hematocrit, a transfusion of whole blood or packed red blood cells is counted as 1 g/dl (0.1 g/l) hemoglobin or 3 % absolute in hematocrit. This would be in addition to the actual fall in hemoglobin or hematocrit.

^*^To account for transfusion, hemoglobin and hematocrit measurements will be adjusted for any packed red blood cells or whole blood given between baseline and posttransfusion measurements. A transfusion of one unit of blood will be assumed to result in an increase of 1 g/dl in Hgb or of 3 % in Hct. Thus, to calculate the true change in Hgb or Hct if there has been an intervening transfusion between two blood measurements, the following calculations should be performed: Hgb =[baseline Hgb-posttransfusion Hgb] + [number of transfused units] Hct = [baseline Hct-posttransfusion Hct] + [number of transfused units × 3].

The following will be classified as “instrumented” major bleeding that is considered to be associated with the catheterization laboratory visit:

- Major percutaneous entry site: bleeding occurred at the percutaneous entry site during or after the catheterization laboratory visit until discharge. The bleeding should require a transfusion and/or prolong the health care facility stay, and/or cause a drop in Hgb >5 g/dl
- Bleeding at the percutaneous entry site can be external, or a hematoma >10 cm for femoral access or >2 cm for radial access, or >5 cm for brachial access

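### Sustained clinical improvement is scored on an ABI level of 0.15 instead of a gain of 0.15, so the ABI half of this secondary end point filters almost nobody; three smaller Appendix wording errors also need correcting

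*Protocol article*

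**What the plan says.** Outcome measures in the protocol article lists ten secondary end points and refers to the Appendix for the detailed definitions. Four definitions in that Appendix matter here.

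- **Sustained clinical improvement** (end point 4; Appendix 1): "persistent ABI value ≥0.15 and persistent improvement of ≥1 class according to Rutherford throughout follow-up", compared with baseline, without repeat TLR, in surviving patients.
- **TLR and TER** (end points 5 and 6; Appendix 1): a repeat procedure counts when it is "performed for restenosis because of a return of ischemic symptoms, decrease of at least one Rutherford category", or for two further alternatives, "decrease in the ankle brachial index of >0.15, or restenosis of >50 % as measured by catheter angiography".
- **Stent fracture grade** (Appendix 1): "minor (single strut fracture), moderate (fracture of more than two struts"; severe means complete separation of the stent segments.
- **Bleeding** (Appendix 5): a major bleed is overt bleeding, or documented intracranial or retroperitoneal hemorrhage, "associated with a drop in hemoglobin (Hgb) of greater than 5 g/dl (0.5 g/l" in brackets, or with a stated fall in hematocrit. The same bracketed conversion appears in the minor category. The transfusion note equates 1 g/dl with 0.1 g/l.

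For comparison, Appendix 2 words acute hemodynamic success as a gain: "defined as a ≥0.15 improvement in the ankle-brachial index from preprocedure to immediately postprocedure (discharge".

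**The concern.** An ABI is ankle pressure divided by the highest arm pressure (Appendix 4). A level of 0.15 is therefore very low, and a patient can reach it without benefiting from the stent. If the definition is applied as written, patients whose Rutherford class improves but whose ABI does not would be counted as sustained improvers. The hemodynamic confirmation that the definition appears to call for would be lost, in both arms.

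The other three items are of the same kind but weigh less. The Rutherford wording in TLR and TER points the wrong way. The fracture grades leave one strut count without a category. The g/l figures in the bleeding definitions are arithmetically wrong. TLR also enters the Appendix definitions of sustained clinical improvement and of MACE, so its wording carries into those outcomes.

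**Working it through.** **1. ABI: level or change**

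| Place | Use of 0.15 |
|---|---|
| Appendix 1, sustained clinical improvement | a *value* of at least 0.15 |
| Appendix 1, TLR and TER | a fall of more than 0.15 |
| Appendix 2, acute hemodynamic success | an improvement of at least 0.15 |

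Only the first is worded as a level. To show what that level means, assume an arm pressure of 130 mmHg (not in the protocol): 0.15 × 130 = 19.5 mmHg at the ankle.

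The protocol gives no baseline ABI, so take an assumed range of 0.30 to 0.70. The gain rule requires baseline + 0.15.

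| Assumed baseline | Level rule met with no change? | ABI needed under a gain rule |
|---|---|---|
| 0.30 | yes | 0.45 |
| 0.40 | yes | 0.55 |
| 0.50 | yes | 0.65 |
| 0.60 | yes | 0.75 |
| 0.70 | yes | 0.85 |

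The direction of the error does not depend on these assumptions. A baseline ABI cannot be below 0, so a gain of at least 0.15 always produces a value of at least 0.15. Everyone who passes the gain rule also passes the level rule, and the reverse is not true. The rate under the literal wording is therefore equal to or higher than the rate under a gain rule.

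**2. Rutherford direction**

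Study population assigns scores 2 to 3 to claudication, 4 to rest pain and 5 to 6 to ischemic ulcers, so a higher score is worse. TLR and TER list a decrease of a category beside recurrent symptoms and a falling ABI as a reason for repeat revascularization. On the protocol's own scale a decrease is an improvement. The four reasons are alternatives joined by *or*.

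**3. Fracture grades by number of struts (no complete separation)**

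1 strut: minor. 2 struts: no grade. 3 or more: moderate. The listed end point (2) is the incidence of fracture, and a two-strut fracture counts towards it.

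**4. Hemoglobin units**

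g/l = 10 × g/dl.

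- 5 g/dl × 10 = 50 g/l; the protocol states 0.5 g/l; 50 / 0.5 = 100.
- 1 g/dl × 10 = 10 g/l; the protocol states 0.1 g/l; 10 / 0.1 = 100.

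Read backwards, 0.5 g/l is 0.5 / 10 = 0.05 g/dl. The stated conversions do not reproduce; each is too low by a factor of exactly 100.

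**The case against.** The strongest defense of the ABI wording is that the sentence goes on to mention a comparison with baseline, and that the rest of the Appendix uses 0.15 only as a change. A reader can therefore work out that a gain was probably meant. That stands as evidence of intent. It does not repair the text: the comparison attaches most naturally to the Rutherford clause, and the noun in the ABI clause is still *value*. It is also fair that only the ABI half loses its force. A patient must still keep an improvement of at least one Rutherford class and avoid repeat TLR. Nothing shows that sites are applying the literal reading.

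A reader might infer that all four slips would misclassify outcomes. The document does not support that for the other three.

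- **TLR and TER.** A patient who worsens and is re-treated would normally qualify through recurrent symptoms, an ABI fall or restenosis above 50 %. Few events, if any, would be lost.
- **Fracture.** The gap does not damage the safety end point, which is incidence. Grade appears only in the Appendix. The document also cannot say whether two struts belong to minor or moderate, because the grading is taken from a cited source.
- **Bleeding.** It would be wrong to say that trivial hemoglobin falls become major bleeds. A major bleed also needs overt bleeding or documented intracranial or retroperitoneal hemorrhage. The g/dl figure comes first in each definition, and the adjustment formula and the catheterization-related criteria work in g/dl. Bleeding is not among the ten secondary end points. An error needs someone to ignore the g/dl figure and use the bracket.

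**Conclusion.** The ABI point holds and is the substance of this finding. As written, the ABI condition for secondary end point (4) is met without any gain at every assumed baseline from 0.30 to 0.70. The end point then reduces in practice to Rutherford improvement without repeat TLR, and its rate would be inflated. How far cannot be computed, because the protocol gives no ABI distribution and no expected rate for this end point. The conclusion assumes that the definition is applied literally.

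The Rutherford direction, the two-strut gap and the g/l conversions are real errors in the text, but they could only occasionally change a classification. None of the four touches the primary patency end point, the noninferiority margin or the sample size, and none should be read as a threat to the trial's main conclusion.

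**What to change.** **Main change.** In Appendix 1, replace the ABI clause of sustained clinical improvement with *persistent ABI increase of at least 0.15 compared with baseline*, in line with Appendix 2. The observed rate will be lower than under the literal rule.

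**Minor corrections.**

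- In TLR and TER, replace the Rutherford clause with *worsening (increase) of at least one Rutherford category*, consistent with Study population.
- In Appendix 5, correct the brackets to 50 g/l for 5 g/dl (in both the major and the minor category) and 10 g/l for 1 g/dl, or delete them and keep g/dl as the only unit.
- Close the two-strut gap by reconciling the grades with the grading source that the Appendix cites, and state that the incidence of any fracture is unaffected.

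**Cost.** Wording in the Appendix, the case report form and the event adjudication criteria. ABI is already needed before the procedure for acute hemodynamic success and is planned at 1, 6 and 12 months, so no new data are required. The article describes the trial as still recruiting. Making the change before outcomes are analyzed avoids choosing a definition after the results are known.
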